### Data analysis

This study is a phase I/II, single-blinded study, involving the use of an investigational new drug, conducted at The Rockefeller University Hospital. As such, this plan is written in accordance with FDA regulations on IND safety reports and annual reports (title 21 part 312.32 & 33), and ICH’s Good Clinical Practice Guidelines. This plan also meets NIH and NCI policies (NIH Policy for Data and Safety Monitoring, Further Guidance on a Data and Safety Monitoring for Phase I and II Trials, NCI Essential Elements of a Data Safety and Monitoring Plan for Clinical Trials Funded by the NCI), in the event the study receives such funding.

#### Analysis of safety data.

##### Quantitation of toxicity data.

Local reactions are measured in quantitative measures of pain, induration and redness. This data will be tabulated and monitored in order to be able to report on the quantitative extent of discomfort resulting from vaccination.

Systemic reactions are quantitated on a severity scale of grade I-IV. All reactions will be recorded and the percentage of reactions of each grade tabulated relative to the number of patient inoculations to determine frequency of adverse systemic reactions.

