### Objectives

The primary objective in this Phase 1 study will be to ascertain the safety of the DC/LNCaP vaccine. More precisely, the study will monitor the safety of employing *ex vivo* generated autologous dendritic cells (DCs) pulsed with apoptotic prostate cancer cells as a therapeutic in prostate cancer patients.

An additional objective of this study is to evaluate the immunogenicity of autologous DCs pulsed with apoptotic prostate cancer cells. The primary immunogen in this study, the DC/LNCaP vaccine, does not harbor known antigens to which predictable immune responses can be studied and definitively be attributed to the vaccination. For this reason, patients will be immunized with the DC/LNCaP-M1 vaccine in separate subcutaneous inoculations at the time of immunization with the DC/LNCaP vaccine. This positive control immunogen harbors an antigen, the influenza matrix antigen, to which most patients have been exposed, and to which baseline and post-immunization responses can be monitored. In this way, the study is designed to yield definitive information regarding immunogenicity of autologous DCs presenting antigen derived from apoptotic tumor cells. Because of the theoretical concern that the overexpressed M1 epitopes might displace endogenous prostate tumor epitpoes, the vaccination will be split between “pure” DC/LNCaP cells and the DC/LNCaP-M1 vaccine control.

Secondary objectives in this study will be the evaluation of the clinical course of immunized patients. This will include both subjective analysis of patient symptoms, and objective analysis of clinical tests performed before and after vaccination. Any analysis of clinical or immunologic data obtained from patients who do receive conventional therapy after vaccination will need to be evaluated with this variable taken into consideration.

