###### On-study evaluations

Entry (Week 0)

Entry day is defined as the day of leukapheresis, which is performed 8-9 days (preferably 8 days) prior to the first immunization (which occurs on “Week 1”).

Directed History and Physical: The Principal Investigator or his designee will perform a directed history and physical, with the aim of assessing any new or unresolved signs and symptoms experienced since the last visit.

At baseline (week 0) all signs and symptoms will be recorded on the CRF. For post-baseline assessments (week 1 and subsequently), all Grade 2 or higher signs/symptoms will be recorded on the CRF. Please see Table 3 for grading of local reactions to vaccines.

Any signs or symptoms that lead to a change in treatment, regardless of grade, must be recorded on the CRFs.

Leukapheresis. All subjects in Arm 1 undergo leukapheresis at entry (“Week 0”) and all subjects in Arm 2 undergo leukapheresis at Week 0 and 8. Post treatment, all patients will undergo another leukapheresis. In the event we cannot use a leukapheresate, such as due to a poor cell yield or a contamination, the procedure may be repeated. Alternatively, in such an event, previously frozen down monocytes if available may be used to prepare the vaccine.

This procedure will be performed at The Rockefeller University GCRC.

Note: Hematology evaluations are required within 1 week prior to the leukapheresis.

100 cc of whole blood will be drawn for making autologous plasma on Week 0. White blood cells from this blood may be stored and used for additional assessment of baseline immunologic function (e.g. allogeneic mixed lymphocyte reactions, allo-MLR).

Week 1, 3, 5, 7 (Arm 1) and week 1, 3, 5, 7, 9, 11, 13, 15 (Arm 2)

History and physical, and indicated blood draws must occur prior to study vaccination.

Vaccination:

Arm 1 (up-front vaccine):

Weeks 1, 3, 5 and 7 autologous DCs co-cultured with apoptotic irradiated LNCaP cells are given SQ in single injections of 500 l. At each of these times, autologous DCs co-cultured with apoptotic irradiated LNCaP-M1 cells, as well as either saline or vaccine vehicle alone (5% DMSOin normal saline) are given SQ in single injections of 500 l. On weeks 1 and 3, autologous DCs exposed to KLH are also given SQ. The SQ injections may be given +/- 3 days from the scheduled visit, with the exception that the first injection, which will be given on day 8 (preferably) or day 9 after the patient completes leukapheresis.

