Arm 2 (placebo followed by vaccine):

Weeks 1, 3, 5 and 7 Either saline or vaccine vehicle alone (5% DMSO in sterile saline) is given SQ in single injections of 500 l. At week 9, 11, 13, and 15 autologous DCs co-cultured with apoptotic irradiated LNCaP cells are given SQ in single injections of 500 l. At each of these latter times, autologous DCs co-cultured with apoptotic irradiated LNCaP-M1 cells, as well as either saline or vaccine vehicle alone (5% DMSOin normal saline ) are given SQ in single injections of 500 l. On weeks 9 and 11, autologous DCs exposed to KLH are also given SQ. The SQ injections may be given +/- 3 days from the scheduled visit, with the exception that the first injection, which will be given on day 8 (preferably) or day 9 after the patient completes leukapheresis.

Administration of Vaccine

The DC/LNCaP vaccine is given approximately 6-8 cm from the axilla in the inner aspect of the upper arm. The DC/LNCaP-M1 vaccine is given approximately 6-8 cm from the axilla in the inner aspect of the patients’ contralateral upper arm. The administration site is prepared with betadine and alcohol swabs. Injection is given with a 25-gauge needle by superficial SQ injection (not in the fatty part). DCs exposed to KLH and either saline or vaccine vehicle alone may be given in the anteromedial thigh approximately 12-24 cm distal to the inguinal ligament.

Immunologic Studies

DTH: DTH will be performed at the Rockefeller University GCRC, concurrent with each vaccination and at 2 weeks, 10 weeks and in some patients, at 22 weeks post last vaccination. DTH reactions will be read at the Rockefeller University GCRC between 40-48 hours after implantation. Results will be recorded on the CRF.

Lymphoproliferative responses, ELISPOT and CTL: Assays will be performed at the Rockefeller University.

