##### Quantitation of clinical immunologic data.

Specific measures of autoimmune response will be tabulated and monitored in order to be able to report on the quantitative extent of elevation of autoimmune immunologic parameters. These include serial measurements of ANA, dsDNA, and RF. Severity of reactions will be graded on a scale of I-IV, and results tabulated relative to the number of patient inoculations to determine frequency of elevation of autoimmune immunologic parameters.

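### Systemic reactions and autoantibody elevations are tabulated per inoculation, an undefined unit that understates risk per patient and may be unequal between the arms

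*Combined protocol and SAP*

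**What the plan says.** Section (6)i.n, under quantitation of toxicity data, presents systemic reactions by grade as a "percentage of reactions of each grade tabulated relative to the number of patient inoculations to determine frequency of adverse systemic reactions". The next subsection grades elevations of ANA, dsDNA and RF and has "results tabulated relative to the number of patient inoculations to determine frequency of elevation of autoimmune immunologic parameters". Neither subsection defines an inoculation, says whether a companion saline or vehicle injection counts, or says whether the tables are split by arm or period.

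The dosing text under on-study evaluations gives several injections per visit in Arm 1:

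- "Weeks 1, 3, 5 and 7 autologous DCs co-cultured with apoptotic irradiated LNCaP cells are given SQ in single injections"
- "At each of these times, autologous DCs co-cultured with apoptotic irradiated LNCaP-M1 cells, as well as either saline or vaccine vehicle alone"
- "On weeks 1 and 3, autologous DCs exposed to KLH are also given SQ"

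For the placebo phase of Arm 2 it says: "Weeks 1, 3, 5 and 7 Either saline or vaccine vehicle alone (5% DMSO in sterile saline) is given SQ in single injections".

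The Objectives section comes closest to showing what the word means. It describes giving the "DC/LNCaP-M1 vaccine in separate subcutaneous inoculations at the time of immunization with the DC/LNCaP vaccine", so several inoculations can make up one immunization.

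**The concern.** A fever or a newly raised ANA happens to a patient. When three or four products are injected at one visit, nothing in the data can tie a systemic event to one of them. A denominator of injections therefore grows with the number of syringes used, without any matching gain in information about risk.

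Two things are at stake. First, the percentage a reader sees will be much smaller than the share of patients affected. Second, if every injection counts, the denominators of the two arms differ although both arms have 12 patients and four visits.

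This matters because safety is the primary objective, and the incidence and severity of adverse events is one of two primary outcomes compared before cross-over. The events in these tables are also of particular interest. The animal toxicity section reports a rise in strongly reactive ANA at the highest cell dose, and Table 5 shows pulmonary vasculitis in 3 of 3 mice at that dose against 0 of 3 controls.

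**Working it through.** **The plan's own figures.** The plan states no rate per inoculation and no total number of injections, so there is none to reproduce. It does give one-sided exact p-values for SAEs, and these show which unit the formal test uses. With 12 patients per arm, the hypergeometric tail gives:

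- 3 v 0: C(12,3)/C(24,3) = 220/2024 = 0.1087 (stated .109)
- 4 v 1: (495×12 + 792)/42504 = 0.1584 (stated .158)
- 5 v 1: (792×12 + 924)/134596 = 0.0775 (stated .077)

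All three match, so the formal SAE comparison counts patients, not injections.

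**Injections per patient before cross-over**, from the dosing text:

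- Arm 1: 4 DC/LNCaP + 4 DC/LNCaP-M1 + 2 DC/KLH + 4 saline or vehicle = 14. That is 4 per visit at weeks 1 and 3, and 3 per visit at weeks 5 and 7.
- Arm 2: 4 placebo injections, one per visit.

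**Denominators for 12 patients per arm, and the share shown when one Arm 1 patient has one event:**

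| Unit | Arm 1 | Arm 2 | Ratio | One Arm 1 event |
| --- | --- | --- | --- | --- |
| Patient | 12 | 12 | 1.0 | 1/12 = 8.3% |
| Visit | 4×12 = 48 | 48 | 1.0 | 1/48 = 2.1% |
| Injection, leaving out the Arm 1 companion saline/vehicle | 10×12 = 120 | 48 | 2.5 | 1/120 = 0.8% |
| Every injection | 14×12 = 168 | 48 | 3.5 | 1/168 = 0.6% |

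So even the visit reading, the most favourable one, shows a quarter of the patient-level figure when each affected patient has one event.

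**Effect on a comparison of arms if every injection counts.** Take one reaction per affected patient.

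- 7 of 12 vaccine and 2 of 12 placebo patients: 7/168 = 4.2% and 2/48 = 4.2%. The table shows no difference, while the one-sided exact test on patients gives (52272 + 5940 + 220)/1307504 = 0.045.
- At the plan's design rates of 50% and 5% of patients, the expected numbers affected are 6 and 0.6. Per injection this is 6/168 = 3.6% against 0.6/48 = 1.25%, a ratio of 2.9 in place of 10. The direction is kept and the contrast is reduced. Per visit it is 12.5% against 1.25%, still 10-fold.

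The order of the arms reverses only when the true ratio of patients affected is above 1 and below 3.5.

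**The case against.** The strongest reply is that the imbalance between arms is conditional. The denominator is undefined, and the schema counts dosing by occasion: one immunization and three boosters, matched by one placebo immunization and three placebo boosters. On that reading the ratio is 1.0. These subsections also describe descriptive tables and announce no comparison of arms. Both points stand. A reader might infer that the plan dilutes vaccine rates 3.5-fold as a matter of fact. The documents do not support that: the Objectives wording, and the mention of a site of inoculation under risks and complications, favour counting each injection, but neither defines the denominator.

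A second reply is that patient-level safety analysis exists elsewhere. This is also true. The Fisher test on SAEs is per patient, the stopping rule counts subjects with dose-limiting toxicity (which includes autoimmune reactions of grade 2 or more), and the benefit score uses each patient's worst adverse event category. A reader might infer that the primary safety decision is biased. It is not, because none of these uses the inoculation denominator.

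What these analyses do not supply is a frequency per patient for non-serious systemic reactions and for autoantibody elevations. The Fisher test covers SAEs only, the stopping rule only dose-limiting events, and the benefit score merges adverse events with PSA. The toxicity endpoint section tabulates all adverse events by body system but names no denominator. For these events, the only stated frequency is the one per inoculation.

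**Conclusion.** The point holds in limited form. The stated frequency has no clear unit. With one event per affected patient it understates the share of patients affected on every reading: 8.3% of patients becomes 2.1% per visit, 0.8% per active injection or 0.6% per injection. The gap narrows if the same patient reacts at several visits.

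Any comparison of arms drawn from these tables is diluted by a factor between 1.0 and 3.5, depending on what an inoculation means. The upper figure assumes that every scheduled subcutaneous injection counts, that all doses are given, and that only the period before cross-over is compared. It leaves out DTH skin tests. Counting those would widen the imbalance, since placebo-phase patients receive saline DTH only.

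This is a should-fix rather than a must-fix. The tables are descriptive, all reactions are to be recorded so patient-level rates can be recovered, and the formal test, the stopping rule and the benefit score would not change. In a trial of 24 patients, however, the descriptive safety tables are among the main results and should be readable as risk per patient.

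**What to change.** In both subsections of (6)i.n, make the patient the unit. Report the number and percent of patients with at least one event, by highest grade, with exact 95% intervals, in two sets:

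- by arm, for the period that ends before the first Arm 2 vaccine injection at week 9, with the same window for Arm 1. A cut-off worded simply as to week 9 could let vaccine events into the placebo column;
- for all patients of both arms while receiving vaccine.

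Rates per visit may be added as a supplement, with the unit defined. Keep rates per injection site for local reactions only, where an event can be tied to a site.

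The cost is a rewording of two sentences, revised table shells and slightly more tabulation. No new data, patients or changes to tests or stopping rules are needed.

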##### Quantitation of clinical immunologic data.

Specific measures of autoimmune response will be tabulated and monitored in order to be able to report on the quantitative extent of elevation of autoimmune immunologic parameters. These include serial measurements of ANA, dsDNA, and RF. Severity of reactions will be graded on a scale of I-IV, and results tabulated relative to the number of patient inoculations to determine frequency of elevation of autoimmune immunologic parameters.

#### Analysis of immunogenicity data.

Immunogenicity data will be tabulated and quantitated for each of the quantitative assays planned. These include proliferation assays, ELISPOT assays, and CTL assays. For example, we will correlate positive or negative responses (proliferation index > 5, ELISPOT T cell responses > 100 SFC/106 T cells, and CTL responses with % specific killing > 15%) with positive or negative responses to our positive control antigens (influenza M1) and, where available, to the prostate antigens PSMA and PAP.

For ELISPOT, CTL response, LPA and DTH, the primary analysis will be based on the change from baseline. Changes in baseline will be summarized by the median and 25th and 75th percentiles, and arms compared with the Wilcoxon rank sum test. Additionally, the longitudinal responses will be examined using generalized estimating equation analyses (to incorporate all the responses on a subject).

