##### Design

A phase I/II, randomized, single blind study. Subjects with prostate cancer with rising PSA levels who have failed conventional therapy are eligible.

A total of 24 patients will be enrolled into one of two Arms of 12 patients each. Subjects will be randomly assigned (1:1) at entry to one of the two vaccination groups.

Patients in Arm 1 will receive one immunization and 3 booster immunizations over the course of the first 7 weeks of study. Patients in Arm 2 will receive a placebo (either saline or vaccine vehicle only (5% DMSO in normal saline) immunization and 3 placebo booster immunizations, and will switch after week 7 to the vaccination arm, where they will receive one immunization and 3 booster immunizations exactly as for patients in Arm 1.

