###### Lymphocyte proliferation assay (LPA)

Lymphocyte proliferative response to specific vaccine component antigens (which include the influenza M1 antigen) and to the control antigen KLH.

Lymphoproliferative responses of subject PBMC or purified CD4+ T cells (MACS columns; Miltenyi Biotech) to antigens and mitogens are measured by incubating 1 x 105 cells per well in 96-well U-bottom plates with serial antigen concentrations of protein, recall antigen (tetanus toxoid, KLH) and in separate plates with serial dilutions of PHA, PWM and ConA. After 3 days of incubation with the mitogens and 6 days with the antigens, cells are pulsed with 1 Ci/well of (3H)-thymidine for 6hr and then harvested using the Tomtec (EG&G Wallac, Gaithersburg, MD) and counted in a 1450 microbeta trilux (EG&G Wallac, Gaithersburg, MD). The data are expressed as an LSI (Lymphocyte stimulation Index = (PBMC cpm + antigen or mitogen)/(PBMC cpm + medium)) to define antigen specificity. Individuals are arbitrarily designated as responders or non-responders if their LSI is greater than or equal to 5.

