### Human efficacy data.

We assessed whether DCs derived from prostate cancer patients are capable of cross-presenting antigen derived from apoptotic LNCaP cells for the activation of antigen-specific T cells. Leukapheresates were obtained from prostate cancer patients under the care of [name] and in accordance with our IRB protocol RDA 0269.

Prostate patient DCs were co-cultured with apoptotic influenza infected and uninfected LNCaP cells and ELISPOT assays were performed. Both influenza-specific CD4+ and CD8+ T cells were detected in 7 out of 7 patients. In addition, DCs obtained from HLA A*0201 prostate cancer patients were co-cultured with apoptotic LNCaP-M1 and used to stimulate T cells for 7 days in vitro, allowing us to determine effector CTL function. Cytotoxicity was measured using influenza matrix-peptide pulsed T2 cells as targets, and demonstrated the presence of M1-specific CTLs in 3/4 HLA A*0201 prostate cancer patients.These results demonstrate that apoptotic LNCaP cells are able to effectively cross-present antigen for the activation of CD4+ and CD8+ T cells. This data is summarized in Table 6 below.

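### Whether assay responses track the M1 control is examined only on yes/no cut-offs of quantitative assays, which discards information with 24 men planned

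*Combined protocol and SAP*

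**What the plan says.** All of the following is from the combined protocol and SAP.

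- **The link with the control.** *Analysis of immunogenicity data* first says that each quantitative assay will be tabulated and quantitated. It then gives an example: "we will correlate positive or negative responses (proliferation index > 5, ELISPOT T cell responses > 100 SFC/106 T cells", plus more than 15% specific killing for CTL, are to be related to M1 and, where available, to PSMA and PAP. The M1 side is also binary: "with positive or negative responses to our positive control antigens (influenza M1". (The 106 is 10^6 with the superscript lost.)
- **The primary immunogenicity analysis.** The next paragraph of that section says: "For ELISPOT, CTL response, LPA and DTH, the primary analysis will be based on the change from baseline". It is summarised by medians and quartiles, with "arms compared with the Wilcoxon rank sum test", and followed over time by GEE.
- **The LPA cut.** *Lymphocyte proliferation assay (LPA)*: "Individuals are arbitrarily designated as responders or non-responders if their LSI is greater than or equal to 5".
- **The purpose of the control.** *Objectives* explains that M1 is an antigen most patients have met, so responses can be followed from before to after immunization, and concludes that "the study is designed to yield definitive information regarding immunogenicity of autologous DCs presenting antigen derived from apoptotic tumor cells".
- **Numbers.** *Design*: "A total of 24 patients will be enrolled into one of two Arms of 12 patients each". Replacement of men who discontinue is allowed (*Criteria for Subject Study Discontinuation*), so 24 is the planned number and not a strict ceiling.

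**The concern.** Stimulation index, spot count and percent killing are all quantitative readings. Cutting both members of a pair turns 24 pairs of values into one 2x2 table. A man just above a cut then counts the same as one far above it, and the ordering within each half is lost.

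The full-scale analysis in the same section compares arms and follows responses over time. It does not relate one response to another. *Interim and Final Analysis* relates the number of dendritic cells given to immunologic responses, which is a different question. The yes/no correlation is therefore the only described analysis of whether other responses rise with the M1 response.

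What is at stake is a false impression of no relationship. The plan's own reasoning points the other way: *Biostatistical analysis* prefers a false positive to a false negative on activity, and uses a rank test for PSA because the form of its relationship with clinical success is unknown.

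M1 may also be an awkward yes/no variable. If most men are positive, one margin of the table is nearly constant and little can be learned from it.

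**Working it through.** The plan gives no power, level, effect size or named test for this correlation, so there is no figure of its own to reproduce. The check asks how much a yes/no cut costs.

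**Inputs from the documents:** n = 24; both sides binary.

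**Assumptions, not in the documents:** bivariate normal responses with correlation rho; the positivity rates; the tests; the levels. One-sided 10% is set in *Biostatistical analysis* for PSA and SAEs only. It is shown here beside two-sided 5% for reference.

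**Method.** Simulate 24 pairs, 20,000 times per setting. Test Spearman's r_s on the values through t = r_s × sqrt((n − 2)/(1 − r_s²)) on 22 degrees of freedom. Cut both variables to give the assumed positivity, then apply Fisher's exact test or an uncorrected chi-square. Loss = Spearman power − 2x2 power.

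**Power (%), both variables 50% positive:**

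| rho | Level | Spearman | Fisher (loss) | Chi-square (loss) |
|---|---|---|---|---|
| 0.4 | two-sided 5% | 46 | 18 (28) | 27 (19) |
| 0.5 | two-sided 5% | 66 | 29 (37) | 40 (26) |
| 0.6 | two-sided 5% | 85 | 44 (41) | 56 (29) |
| 0.4 | one-sided 10% | 72 | 33 (39) | 50 (22) |
| 0.5 | one-sided 10% | 87 | 46 (41) | 63 (24) |
| 0.6 | one-sided 10% | 96 | 62 (34) | 77 (19) |

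**Other mid-range rates.** Over the pairings 50/50, 30/50, 50/70 and 30/30%, with rho 0.4 to 0.6, the losses are about:

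- two-sided 5%: 18 to 37 points (chi-square), 27 to 51 (Fisher);
- one-sided 10%: 19 to 26 (chi-square), 34 to 45 (Fisher).

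These ranges need the two rates to be no more than 20 points apart. With 30% against 70%, the two-sided 5% losses are larger: 31 to 55 (chi-square) and 40 to 71 (Fisher).

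**How much is Fisher's conservatism.** With rho = 0 and 50/50, Fisher rejects 3.0% of the time at nominal 5% and 4.3% at nominal one-sided 10%. Chi-square rejects about 6% and 10%. The chi-square column is therefore the fairer measure of what the cut itself costs.

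**When the loss is smaller (Fisher, 50/50).** At rho 0.8 it is 20 points (two-sided 5%) or 9 (one-sided 10%). If 40% of values sit at an assay floor, it is 12 to 33 or 9 to 36 over rho 0.3 to 0.8.

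**When it is larger.** With M1 positive in 75% and the other assay in 50%, Fisher loses 33, 47 and 56 points at rho 0.4, 0.5 and 0.6 (two-sided 5%). With M1 positive in 90%, Fisher's power is only 2 to 9% over rho 0.3 to 0.8. The chance of at most one M1-negative man is then 0.9^24 + 24 × 0.1 × 0.9^23 = 0.080 + 0.213 = 0.29.

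**The case against.** **The control's main question does not depend on this table.** A reader might infer that the trial can no longer show whether the vaccine was immunologically active. The documents do not support that. *Broad Objectives* and *Objectives* introduce M1 to see whether reactivity to it changes after immunization, and that is analysed as continuous change from baseline. DTH, the primary immunogenicity parameter, is not in the dichotomised sentence. If nearly every man responds to M1, the control has worked. This objection stands and limits the point to the association between responses.

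**Nothing is formally tested.** The sentence is an example, names no test or level, and no decision hangs on it. That stands too: the power figures show the information lost, not the operating characteristics of a planned test. The point survives because no other analysis of the link is described.

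**High M1 positivity is not established.** *Human efficacy data* reports that "Both influenza-specific CD4+ and CD8+ T cells were detected in 7 out of 7 patients". A reader might take this as M1 positivity near 100%. It is influenza-specific detection ex vivo with influenza-infected cells, and it is not stated against the 100 SFC cut. The M1-specific figure there is CTL in 3 of 4 HLA A*0201 patients. A nearly constant margin is possible, not shown.

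**The comparison is idealised.** The simulation cuts and ranks the same values. The plan's cuts apply to response levels, whereas a change from baseline carries error from two measurements. The gain for the proposed replacement is thus indicated, not measured.

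**Readouts are not all on one scale.** *ELISPOT analysis* runs a 7-day recall assay only when the direct assay is negative, and the CTL section has fresh and recalled cells. Pooling them in one rank correlation would be wrong. This stands, and the fix allows for it.

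**Conclusion.** The concern holds as a weakness of a secondary, illustrative analysis. The only described analysis of whether assay responses track M1 (and PSMA or PAP where available) makes both sides yes/no, at cuts of which the plan itself calls one, for LPA, arbitrary.

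The direction of the loss is firm. Its size rests on assumed normality, rho, positivity, test and level: roughly 20 to 35 points from the cut itself at moderate correlation and similar mid-range positivity rates, and more if Fisher's test is used. It is less at very strong correlation or with many floor values, and more if most men are M1-positive or the two rates differ widely. The primary immunogenicity analysis is continuous and needs no change on this account.

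**What to change.** In *Analysis of immunogenicity data*, replace the example with a stated association analysis:

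- Use a Spearman or Kendall rank correlation, with confidence interval, of the quantitative change from baseline in each assay (stimulation index, SFC per 10^6, percent specific killing) against the M1 change and, where available, the PSMA and PAP changes.
- Compute it separately within each assay format: direct and recall ELISPOT, fresh and recalled CTL. Report the number of men in each, and note that recall ELISPOT is run only in men negative on the direct assay.
- Keep the positive/negative cross-tabulation as description only.

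The cost is wording and slightly more analysis work. The assays already yield the quantitative values, so no further patient, sample or assay is needed. The downside is that each format-specific correlation will include fewer than the planned 24 men, so some intervals will be wide.
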